### Power calculation

Power calculation has been performed by a formally trained institutional biostatistician, based on the primary endpoint of the rate of SREs from the date of participant randomization to their death or 12 months follow-up, whichever occurs first, in the two trial arms. SRE, a composite outcome measure, has been defined as a pathological spine fracture, spinal cord compression, or warranting of a procedure (palliative RT, interventional procedures, or spine surgery). SRE is a binary variable, where the event rate may be defined as the number of spine lesions with SRE occurrence divided by the total number of target spine lesions identified. Given the lesion-based analysis in the current trial, occurrence or non-occurrence of an SRE at one vertebra does not impact the status of other spine lesions within the same individual.

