Based on institutional records and previous trials, it is estimated that nearly 60–80% of patients may be successfully followed up for at least 1 year. For the standard of care trial arm, where only routine medical management is done, the rate of SRE is known to be nearly 60% within 1 year. Meanwhile, it is known that approximately three fourths of inpatient radiation consultations for painful bone metastases have been reported to lead to palliative RT. Furthermore, prior studies indicate that nearly 60% of RT-targeted spine lesions had been diagnosed ≥ 4 months prior to RT [7]. Therefore, we believe a 60% estimated event rate (as defined above) at 1 year is a conservative estimate. For the investigational trial arm, where early prophylactic RT is being provided to high-risk spine metastases, an SRE rate of 30% is estimated. The efficacy of RT in controlling pain from spine metastases is well-known. Since RT targets and mitigates, to a certain extent, the pathologic effect of a spinal metastases, this leads to reduced development of major bony pain, which is often a causative factor for SREs. For these SRE rates, inclusion of at least 66 individuals with evaluable SRE endpoints in a 1:1 randomization will allow the trial to achieve > 80% power based on a one-sided, two-sample proportion test with significance level of 0.05. Given that the individuals who withdraw prior to the SRE endpoint occurring may not evaluated as per the trial plan; therefore, a per-protocol analysis will be carried out. The limitations of the per-protocol analysis are mitigated by the use of hard endpoints in the current study along with the high morbidity and dismal prognosis of the participants. In order to ensure a minimum of 33 participants are enrolled per trial arm, we plan to over-accrue by 10%, so that the trial is sufficiently powered for the primary endpoint, resulting in a planned sample size of *N* = 74 participants. Additionally, we note that the unit of analysis is the spine lesion, and a small subset of patients may have multiple evaluable lesions (SREs). Since each lesion will be included separately in the analysis, therefore, the final sample size for the primary endpoint may be higher than estimated. We expect to enroll all 74 participants within 2 years.

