### Randomization, blinding, and allocation concealment

Participants are randomized to either the standard of care (arm 1) or early, upfront RT plus standard of care (arm 2). At the time of randomization, clinicians fill out the Lesion Identification Worksheet (Supplementary file 2: Appendix 2) to document the ≤ 5 high-risk spine metastases per protocol definition to be followed during the protocol in both arms. Once the participant’s eligibility is established, the registration is finalized, and the participants are randomized by the statistician for the study. Randomization is accomplished by the method of a random permuted block and stratified by disease histology (breast and prostate vs. other solid tumors) and planned standard of care treatment (observation vs. systemic therapy). After the treatment arm is determined by randomization, the research coordinator notifies the investigator of the treatment arm within 24 h of randomization. We employ allocation concealment by hiding the allocation sequence from which participants are assigned to the groups until the assignment to prevent selection bias. Both the treating physician and the participant are informed about the treatment they are receiving.

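### The per-protocol primary analysis may drop patients who withdraw without an SRE but keeps those who withdraw after one, so inclusion depends on the outcome and the arm comparison is open to bias

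*Protocol article*

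**What the plan says.** The second paragraph of the Power calculation section sets the analysis population for the primary endpoint: "individuals who withdraw prior to the SRE endpoint occurring may not evaluated as per the trial plan; therefore, a per-protocol analysis" will be carried out. It then defends the choice: "The limitations of the per-protocol analysis are mitigated by the use of hard endpoints", adding the patients' high morbidity and poor prognosis.

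The first paragraph of the same section runs the endpoint window "from the date of participant randomization to their death or 12 months follow-up, whichever occurs first" and defines the event rate as lesions with an SRE over all target lesions identified. Planned statistical analysis repeats this with all eligible spine lesions as the denominator and does not mention a per-protocol set. It describes the two groups by the treatment they receive. The article names no all-randomised analysis of the primary endpoint.

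Under Randomization, blinding, and allocation concealment, up to five lesions per patient are listed on a worksheet at randomisation in both arms, and the trial is open label: "Both the treating physician and the participant are informed about the treatment they are receiving".

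**The concern.** Take two patients who both leave in month 3. One had an SRE in month 2 and is counted as an event. The other had none and may be left out, so the event-free time is lost. Removing people because they had no event raises the SRE proportion in each arm.

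Whether the difference between arms is also distorted depends on who withdraws. In an open-label trial, patients in the two arms may leave at different rates or for different reasons, and randomisation no longer protects the comparison.

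The defence offered does not meet this. A hard endpoint limits misclassification of events; it does nothing about selection after randomisation. Poor prognosis makes loss more likely. Nor is every component hard: the composite includes palliative RT, which is decided by clinicians who know the arm.

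The rule also conflicts with the stated denominator. A rate over all target lesions cannot be calculated after the lesions of event-free withdrawers have been removed.

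**Working it through.** **Inputs from the article (Power calculation).** Control SRE rate 60% at 1 year ("we believe a 60% estimated event rate (as defined above) at 1 year is a conservative estimate"); RT arm: "an SRE rate of 30% is estimated"; one-sided alpha 0.05; 66 evaluable patients; 10% over-accrual to 74.

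**Assumptions of this check.** One lesion per patient; exponential time to SRE; independent exponential withdrawal with 12-month probability *w*; every event-free withdrawer dropped; no deaths. The article gives no withdrawal rate, so *w* is varied from 10% to 40%.

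**1. The planned size.** Two-sample proportion test, pooled variance, one-sided:

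n = [1.645·√(2·0.45·0.55) + 0.842·√(0.24 + 0.21)]² / 0.30² = 32.9, so 33 per arm and 66 in total. Power at 33 per arm is 0.801, and 66/0.9 = 73.3 rounds up to 74. The stated figures reproduce and are not in question.

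**2. What the exclusion rule does to each arm.** With p the true 12-month risk, a = −ln(1−p) and b = −ln(1−w):

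- retained with an SRE: E = a/(a+b) · [1 − (1−p)(1−w)]
- retained without an SRE: N = (1−p)(1−w)
- apparent rate = E/(E+N); share dropped = 1 − E − N

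Example, p = 60%, w = 40%: a = 0.916, b = 0.511, E = 0.488, N = 0.240, apparent rate 0.488/0.728 = 67.0%, dropped 27.2%.

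Example, p = 30%, w = 40%: a = 0.357, b = 0.511, E = 0.2385, N = 0.420, apparent rate 0.2385/0.6585 = 36.2%, dropped 34.2%.

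| w, both arms | Control (true 60%) | RT (true 30%) | Difference (true 30 points) | Dropped, control / RT |
|---|---|---|---|---|
| 10% | 61.5% | 31.2% | 30.3 | 6.6% / 8.4% |
| 20% | 63.1% | 32.6% | 30.5 | 13.3% / 16.9% |
| 30% | 64.9% | 34.2% | 30.7 | 20.2% / 25.5% |
| 40% | 67.0% | 36.2% | 30.8 | 27.2% / 34.2% |

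Both rates rise, but the difference moves by less than 1 point. The share dropped differs by arm even when withdrawal does not, because the arm with fewer SREs has more people left to drop.

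**3. Unequal withdrawal.**

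| True rates | w control / RT | Apparent rates | Apparent difference (points) |
|---|---|---|---|
| 60% / 60% | 40% / 20% | 67.0% / 63.1% | +3.9 |
| 60% / 60% | 20% / 40% | 63.1% / 67.0% | −3.9 |
| 60% / 30% | 40% / 20% | 67.0% / 32.6% | 34.4 |
| 60% / 30% | 20% / 40% | 63.1% / 36.2% | 26.9 |

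**4. Type I error.** Simulation with 37 randomised per arm, 100,000 runs, pooled z test, nominal one-sided 0.05, 60% in both arms: about 0.051 with 30% withdrawal in each arm, 0.094 with 40% control / 20% RT, and 0.026 with the reverse.

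**The case against.** The strongest reply is that the harm is conditional. With equal, non-informative withdrawal the difference and the type I error barely change. The text says such patients may not be evaluated, which permits exclusion rather than ordering it in every case. The only loss allowance tied to evaluability is 10%; a 15% / 5% split around it, with 60% in both arms, gives 0.5606/0.9006 = 62.2% against 0.5871/0.9671 = 60.7%, about 1.5 points. All of this stands. It limits the claim but does not justify a primary analysis whose membership depends on the outcome, and leaving the exclusion optional in an open-label trial is itself a weakness.

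Three stronger readings are tempting, and the document supports none of them.

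- *The comparison is biased.* A reader might infer this, but material bias needs withdrawal that differs by arm or is linked to prognosis. That is plausible, not shown.
- *Withdrawal will be 20–40%, enough to match a clinically relevant effect.* The article expects 60–80% of patients to be followed for a year, but does not separate deaths from withdrawals, and deaths fall inside the endpoint window. Even 40% versus 10% withdrawal, with 45% in both arms, gives 52% versus 46%: about 6 points, a fifth of the 30-point design effect. The article names no smaller relevant difference.
- *Counting an early death as no SRE is a further error.* The window is openly defined to end at death. A cumulative incidence with death as a competing event counts such a patient in the same way. With a latent 45% risk and assumed 1-year mortality of 40% or 20%, it gives (0.5978/1.1087)·0.670 = 36% or (0.5978/0.8209)·0.560 = 41%, the same as the simple count.

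**Conclusion.** The point holds in a limited form. The stated analysis set makes inclusion depend on the outcome, the defence given for it does not address selection, and it contradicts the all-lesions denominator in the first paragraph of Power calculation and in Planned statistical analysis.

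Wherever the exclusion is applied, each arm's SRE proportion is inflated: by about 1 to 7 points at 10–40% withdrawal. The between-arm difference is open to bias of unknown size and direction, from under 1 point with equal non-informative withdrawal to about 4 points either way with a 40% / 20% split. These sizes rest on assumed withdrawal rates, exponential independent times and one lesion per patient. Withdrawal related to prognosis was not modelled.

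It should be corrected before analysis because the rule governs the headline result.

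**What to change.** Make the primary analysis all randomised patients and all lesions on the worksheet, by allocated arm. Analyse time from randomisation to first SRE per lesion, censored at withdrawal or last contact, with SRE-free death as a competing event, in keeping with the stated window to death or 12 months. Compare 12-month cumulative incidence with inference clustered by patient. Add a sensitivity analysis for informative withdrawal and keep per-protocol as supportive.

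Delete the sentence claiming that hard endpoints mitigate the limitations, and reconcile the per-protocol statement with the denominators in Power calculation and Planned statistical analysis.

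The cost is wording and slightly more programming. SREs are recorded whenever they occur (Schedule of assessments, Table 2 footnote) and overall survival requires death dates. The article does not say that withdrawal or last-contact dates are recorded, so this must be confirmed. The planned 74 need not change on this account: on the article's own test, with 37 per arm and all outcomes known, one-sided power at 60% versus 30% would be 0.840. Censoring would take it below that.

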**Methods:**

This is a single-center, parallel-arm, in-progress RCT in adults (≥ 18 years) with ECOG performance status 0–2 and asymptomatic or minimally symptomatic (not requiring opioids) high-risk spine metastases from histologically confirmed solid tumor malignancies with > 5 sites of metastatic disease on cross-sectional imaging. High-risk spine metastases are defined by the following: (a) bulkiest disease sites ≥ 2 cm; (b) junctional disease (occiput to C2, C7-T1, T12-L2, L5-S1); (c) posterior element involvement; or (d) vertebral body compression deformity > 50%. Patients are randomized 1:1 to receive either standard-of-care systemic therapy (arm 1) or upfront, early radiotherapy to ≤ 5 high-risk spine lesions plus standard-of-care systemic therapy (arm 2), in the form of 20–30 Gy of radiation in 2–10 fractions. The primary endpoint is SRE, a composite outcome including spinal fracture, spinal cord compression, need for palliative radiotherapy, interventional procedures, or spinal surgery. Secondary endpoints include (1) surrogates of health care cost, including the number and duration of SRE-related hospitalizations; (2) overall survival; (3) pain-free survival; and (4) quality of life. Study instruments will be captured pre-treatment, at baseline, during treatment, and at 1, 3, 6, 12, and 24 months post-treatment. The trial aims to accrue 74 patients over 2 years to achieve > 80% power in detecting difference using two-sample proportion test with alpha < 0.05.

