### Study endpoints

The endpoints selected in this trial have been utilized by similar trials [10, 14] and are defined within the time window from the date of randomization to death or 12 months, whichever occurs first. The primary endpoint of the study is the number of SREs per arm, which is defined as pathological fractures, spinal cord compression, or interventions (palliative RT, interventional procedures, or spine surgery) at 12 months. The secondary endpoints are as follows:Surrogates of health care cost, including the number and the duration of hospitalizations for SREsPain, as assessed using Brief Pain Inventory (BPI) short-form questionnaireHealth-related quality of life, as assessed using the Functional Assessment of Cancer Therapy-General (FACT-G) and the 5-level EuroQoL-5D (EQ-5D-5L)Median pain-free survival (PFS), defined as the time from study entry to the start of opioids or death. This definition has been utilized on basis of Rosen et al. [10]Median overall survival (OS), defined as the time from study entry to death or censoring due to follow-up

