### Rationale for study instruments and endpoints

This trial is investigating the impact of early, upfront RT on the number of SREs occurring in participants with high-risk spine metastases. The clinical rationale for using SREs as the primary endpoint has been addressed previously and is further expanded here. It has been demonstrated that once a patient’s spinal metastases become severely symptomatic, it is significantly more difficult to return the patient to a low pain burden with treatment compared to when the lesions were less symptomatic [7]. Additionally, in a recent multicenter study that aimed to describe differences in health resource utilization of SREs across Europe and the USA, nearly 25% of reported SREs were found to warrant inpatient hospitalization with a mean length of stay of 18 days [12]. In this work, over 95% of SREs led to procedural management, of which bone RT was the most frequent. Similarly, another investigation demonstrated that nearly a quarter of all SREs warranted an inpatient admission with a mean length of stay of 19.5 days [13]. Furthermore, it has also been demonstrated that efforts to prevent SREs from occurring considerably lead to cost-reduction related to managing SREs, given the substantial economic cost of interventions warranted [11]. Finally, these events also lead to significant utilization of health resources and a major socioeconomic burden [12, 13]. Therefore, on basis of their clinical, economic, and patient-centric utility, SREs have been chosen as the primary endpoint.

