### Planned statistical analysis

The primary objective of this study is to compare the rate of SREs from the date of randomization to mortality or 1 year, whichever occurs first, between participants receiving standard of care therapies versus participants receiving palliative RT for high-risk spine metastases. It is expected that nearly 60% of the enrolled participants will have at least 1 year of follow-up. The primary endpoint, SRE, has been previously defined as a composite measure including pathological spine fractures, spinal cord compression, or need of spinal interventions (palliative RT, or orthopedic surgery). SRE is a binary variable, with the rate of SRE defined as the number of lesions having SRE divided by the total number of eligible spine lesions. Given that this analysis is lesion-based, not participant-based, therefore, occurrence or non-occurrence at one lesion does not impact the status of other lesions in the same participant. Around 15% of participants may have multiple lesions, for which each lesion gets evaluated as an independent unit of analysis. Meanwhile, unlike the primary objective, the secondary objectives will be evaluated per participant.

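### The endpoint called hard includes palliative RT ordered by unblinded physicians, and the article does not say how RT to a still asymptomatic control lesion is scored

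*Protocol article*

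**What the plan says.** The Power calculation section plans a per-protocol analysis because participants who withdraw before an SRE may not be evaluated. It then argues that "The limitations of the per-protocol analysis are mitigated by the use of hard endpoints in the current study", and adds the participants' high morbidity and poor prognosis as further mitigation.

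The primary endpoint is worded in four places in the protocol article:

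- Study endpoints: "pathological fractures, spinal cord compression, or interventions (palliative RT, interventional procedures, or spine surgery) at 12 months". Here the intervention itself is the event.
- Power calculation: fracture, cord compression, or "warranting of a procedure (palliative RT, interventional procedures, or spine surgery").
- Abstract, Methods: the composite includes "need for palliative radiotherapy, interventional procedures, or spinal surgery".
- Planned statistical analysis: need of an intervention, with palliative RT and orthopedic surgery listed and interventional procedures left out.

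On blinding, the randomization section says: "Both the treating physician and the participant are informed about the treatment they are receiving".

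The rationale section cites a health-resource study in which "over 95% of SREs led to procedural management, of which bone RT was the most frequent".

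The Planned statistical analysis section describes the experimental group as "participants receiving palliative RT for high-risk spine metastases", so the term that names an SRE component also names the treatment under test.

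**The concern.** A hard endpoint is one whose occurrence does not depend on someone's judgement about the patient. Fracture and cord compression on imaging come close to that. A decision to irradiate does not, least of all when the person deciding knows whether the lesion has already been irradiated. An unirradiated arm 1 lesion may be referred for RT more readily than an arm 2 lesion that has had it, and the Background says that many specialized centers now favor earlier RT.

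If such RT counts as an SRE whatever its indication, two different things share one code: failure of the control strategy, and crossover to the experimental strategy. An imbalance in crossover would then look like a benefit of early RT even if RT changed nothing in the spine. The per-protocol analysis would also lose the safeguard that the article claims for it.

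**Working it through.** **1. The plan's own figure.** Inputs from the Power calculation section: 60% versus 30%, one-sided alpha 0.05, 80% power, 1:1 allocation. With the pooled-variance formula, pooled rate 0.45:

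n per arm = [1.645 × √(2 × 0.45 × 0.55) + 0.842 × √(0.6 × 0.4 + 0.3 × 0.7)]² / 0.30² = 32.9, rounded up to 33.

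That is 66 in total, with power 80.1% at 33 per arm. Inflation: 66 / 0.9 = 73.3, rounded up to 74. The stated 66 and 74 reproduce, so the arithmetic is not at fault. The question is what the event measures.

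**2. Is there a criterion for RT as an event?** The four wordings side by side:

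| Place | What counts | Criterion given |
|---|---|---|
| Study endpoints | the intervention | none |
| Power calculation | a procedure being warranted | none |
| Abstract | need for RT or a procedure | none |
| Planned statistical analysis | need of an intervention | none |

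The nearest text to a criterion is in the Background. It describes usual care as referral for RT only once a lesion is significantly symptomatic or has caused an SRE. That is not carried into any of the four definitions. Footnote 4 to the assessment schedule has an SRE recorded when the protocol-defined criteria are met, which leads back to the same wording. The article names no blinded or independent adjudication of SREs.

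**3. Size, as an illustration.** Let b be the SRE rate in both arms with no true effect. Let e be the net excess in arm 1 from RT given to quiet lesions and scored as SRE. The documents give no value for e, so 5, 10 and 15 points are assumptions. With X₁ ~ Bin(33, b + e) and X₂ ~ Bin(33, b), sum the joint probability over all outcomes where

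z = (X₁ − X₂)/33 ÷ √(2p̄(1 − p̄)/33) > 1.645, with p̄ = (X₁ + X₂)/66.

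| b | e = 0 | e = 5 | e = 10 | e = 15 |
|---|---|---|---|---|
| 30% | 5.2% | 11.4% | 21.4% | 35.3% |
| 45% | 5.4% | 11.5% | 21.5% | 35.2% |
| 60% | 5.2% | 11.1% | 21.4% | 36.8% |

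The same method gives 81% power for the planned 60% versus 30%.

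**4. The same illustration as a share of lesions.** If a share c of otherwise event-free control lesions is irradiated and scored, the arm 1 rate is b + (1 − b)c. At b = 30%:

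- c = 10% gives 30 + 70 × 0.10 = 37% and a 14.9% chance of a positive result.
- c = 20% gives 30 + 70 × 0.20 = 44% and a 32.3% chance.

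Both tables assume one lesion per patient.

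**The case against.** Two stronger readings are tempting, and the documents support neither.

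**That crossover RT is scored as a control failure.** A reader might infer this from the Study endpoints wording, but no section says so. Need and warranting imply some indication. RT to a quiet arm 1 lesion would depart from usual care as the Background describes it. The per-protocol set is not defined beyond withdrawals, so such a patient might be excluded rather than scored. What stands is that the scoring is unspecified.

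**That most SREs here will be decisions to irradiate.** The cited resource-use study reports how SREs were managed, not which component qualified them as SREs. A fracture that was later irradiated fits its sentence equally well, and most frequent does not mean a majority. The study suggests, but does not show, that RT will be a common component in this trial.

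Three further objections have weight:

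- Counting interventions as SREs follows earlier trials and is a legitimate design choice. That does not make an open-label treatment decision hard.
- The full protocol may hold operational criteria. If so, the article should point to them. The sentence about hard endpoints is a stated argument, not an omission.
- Only the net difference between arms matters. With no true effect, 15 extra points in arm 1 and 10 in arm 2 leave a net 5 points and a chance of about 11-12%, not 35-37%.

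Making a documented trigger a condition of the primary endpoint is also open to dispute. After month 1, scheduled imaging, neurological examination and pain rating fall only at 3, 6, 12 and 24 months. Assessments at the time of an SRE are optional. Genuine events between visits could lack a record, and a pain trigger would still be self-report by an unblinded patient.

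**Conclusion.** The point holds in a limited form. The article is wrong to treat the endpoint as hard and to rely on that to offset the limits of the per-protocol analysis. Palliative RT is a component under all four wordings, the decision is unblinded, and no criterion is stated. How RT to a still asymptomatic arm 1 lesion is scored is left open. If it is scored as an SRE, a referral imbalance biases the primary comparison toward RT.

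The size is conditional. A net excess of 5, 10 or 15 points in arm 1 moves the one-sided false-positive rate from about 5% to about 11%, 21% or 35-37%. This assumes no true effect, 33 lesions per arm, one lesion per patient and a common rate of 30-60%. The excess itself is assumed, and the documents neither support nor exclude it. The planned sample size is not in question here.

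**What to change.** 1. Delete the hard-endpoint justification from the Power calculation section.
2. Reconcile the SRE wording in the abstract, Study endpoints, Power calculation and Planned statistical analysis. State there how RT or a procedure at a listed lesion is scored when no indication arising after randomization is documented.
3. Record the indication for each RT course or procedure on the SRE form.
4. Report the SRE components by arm, and separately RT without a documented indication by arm.
5. Add two sensitivity analyses: (a) RT without a documented indication is not counted; (b) the endpoint is restricted to fracture, cord compression and surgery.

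The clinical threshold for giving RT stays with the investigators; these changes concern scoring and reporting only.

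The cost is one extra form field and some additional analysis. The sensitivity analyses will have fewer events and so less precision. Events between visits may lack documentation, so (a) may discard some genuine events and should be read beside the primary result rather than in place of it.
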